**Figure 1 figure1:**
[figure not shown]
Participant identification, recruitment, and allocation. ART: antiretroviral therapy; REDCap: Research Electronic Data Capture; SMAQ: Simplified Medication Adherence Questionnaire.

During 16 weeks from the date of enrollment, participants receive up to 3 intervention messages per week; they are requested to reply briefly once they read those messages. Weekly, the data manager schedules the delivery of messages according to participants’ preferences, as recorded on REDCap, and monthly questionnaires. During the study, participants can chat with 2 medical doctors on the web-based study platform to ask about health issues, navigate the health system, and schedule infectious disease outpatient consultations (the standard of care requires in-person scheduling). If a participant requests modifications or additions to self-designed messages during the chat, the physician responsible for monitoring the chat will review the new messages initially. The PI will be notified if any content is deemed harmful or inappropriate. He will then contact the participant to explain the reasons for rejecting the message and will request an alternative message. This review process will continue with oversight from the data manager until the accepted messages are included in the platform’s system. Additionally, if physicians responsible for monitoring the platform identify inappropriate content during chat conversations, they will address this with all parties involved non-punitively and constructively. They will explain why the content is inappropriate and direct the conversation to ensure it remains safe and respectful.

As a follow-up, participants receive WhatsApp questionnaires every 4 weeks after enrollment and 2 days apart to assess (1) adherence to ART and (2) user experience with the intervention delivery. After 16 weeks of intervention, participants receive a final message acknowledging their participation and reminding them that the messages will stop.

Participants may withdraw from the intervention at any time by sending a message through the chat platform, responding to messages sent as part of the intervention, or contacting research team members during a medication pick-up visit. The participant will be told that withdrawing from the study does not affect their usual care at the study center. The data manager will register that patient as “withdrawn” in REDCap, and no more messages will be sent.

No concomitant care or interventions are precluded for study participants.

### Sample Size Determination

The sample size calculus considered a 95% CI and the assumption of a 10% difference in optimal ART adherence between study groups (90% in the self-designed group versus 80% in the standardized group by the end of the study). Accounting for a power level of 78.9%, the obtained result was 120 (EPIDAT 4.0). To account for a 2-week pilot phase, we increased the sample size to 131 participants.

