**Methods:**

A 2-arm randomized controlled trial with a parallel assignment of 1:1, with no blinding of study intervention, was performed. Eligible participants are consenting people living with HIV aged 18-29 years who receive HIV care at the study center and whose mobile phones support WhatsApp. Following informed consent and a baseline survey on clinical and personal preferences (eg, timing and frequency of messages), participants are randomized to the control group (messages designed by the research team) or to the experimental group (messages designed by participants), stratified by sex, educational level, current ART intake, and history of ART abandonment. Participants in both groups receive up to 3 WhatsApp messages per week for 16 weeks. ART adherence, the primary outcome, is measured using the Simplified Medication Adherence Questionnaire (SMAQ) at 4, 8, 12, and 16 weeks. Monthly feedback questionnaires on user experience are also administered. The WhatsApp chat format allows two-way communication between participants and the research team throughout the study. We will compare ART adherence between 2 groups at 16 weeks under the intention-to-treat principle, with no interim analysis planned. Based on an estimated 10% difference in adherence, 78.9% power, and a 2-sided α of .05, the target sample size was set at 120, later increased to 131 to include a 2-week pilot phase.

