### Study Design

A randomized controlled trial with 2 arms and a 1:1 assignment ratio will be conducted.

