The study also has limitations. First, as in many other studies, we use a self-reported measurement of medication adherence; extensive use does not assure full accuracy for outcome measurement. We will compare SMAQ results to viral load and CD4 lymphocyte measurements when available to address this. Limitations inherent to the local health system might prevent participants from having up-to-date results of these objective indicators, which restricts the availability of more substantial outcomes related to HIV care. Second, the sample size corresponds to a 10% difference between study groups under the assumption that participants will respond to the final adherence questionnaire, which may not be the case. Third, despite the stratified randomization, it may not be possible to identify if a particular subgroup will benefit more from the intervention. By doing a subgroup analysis of adherence, we will be able to assess the difference in outcomes among subgroups.

To conclude, this study will generate valuable evidence on the use and implementation of mHealth services for young people living with HIV in Peru. If effective, it could inform public policies and improve the quality of care for young people living with HIV.

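### Stated power of 78.9% for 90% versus 80% adherence with 120 participants is wrong; the design gives about 33% (about 36% with all 131)

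*Protocol article*

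**What the plan says.** The calculation appears in three places in the protocol article.

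- **Methods, Sample Size Determination.** The target effect is given as "the assumption of a 10% difference in optimal ART adherence between study groups (90% in the self-designed group versus 80% in the standardized group", at the end of the study. The type I error appears only through "The sample size calculus considered a 95% CI". The result is "Accounting for a power level of 78.9%, the obtained result was 120 (EPIDAT 4.0". The total was then raised to 131 to allow for a 2-week pilot phase.
- **Abstract, Methods.** The same inputs are repeated, now with sidedness: "Based on an estimated 10% difference in adherence, 78.9% power, and a 2-sided α of .05". The target is again 120.
- **Discussion, limitations.** Here "the sample size corresponds to a 10% difference between study groups under the assumption that participants will respond to the final adherence questionnaire", with the caveat that full response may not be achieved.

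Allocation is 1:1 (Study Design). The Data Analysis Plan compares the week-16 proportions by chi-square and by logistic regression. The Results section reports 131 participants enrolled overall.

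**The concern.** Detecting 90% against 80% with close to 80% power normally needs roughly 200 per arm, so 60 per arm looked far too few. A power as unusual as 78.9% also suggests that software returned it for a fixed sample size, which raises the question of what rates were entered.

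This is the primary outcome. The article tells readers that a true 10-point benefit would be detected about four times in five. If the real figure is about one in three, a non-significant result is the likely outcome even when self-designed messages are better by exactly the planned amount. Read against a claimed 78.9%, such a result could be taken as evidence that they are no better. The Discussion says the findings could inform public policy.

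**Working it through.** **Inputs**

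| Input | Value | Source |
|---|---|---|
| Adherence, self-designed / standardized | 0.90 / 0.80 | Sample Size Determination |
| Alpha | 0.05, two-sided (z = 1.960) | Abstract, Methods |
| Allocation | 1:1 | Study Design |
| Sample size | 120 in total, 60 per arm; later 131, 65.5 per arm on average | Sample Size Determination |
| Test | chi-square on two proportions | Data Analysis Plan |
| Stated power | 78.9% | Sample Size Determination; Abstract |

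The numbers 120 and 131 are totals, because Results reports 131 enrolled in all.

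**Formula.** With n per arm, difference d and mean proportion p̄:

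- SE0 = √(2·p̄(1 − p̄)/n)
- SE1 = √([p1(1 − p1) + p2(1 − p2)]/n)
- Power = Φ((d − 1.960·SE0)/SE1)

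**Step 1. Attempt to reproduce the stated power (n = 60, d = 0.10, p̄ = 0.85)**

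- SE0 = √(2 × 0.85 × 0.15/60) = 0.0652
- SE1 = √((0.09 + 0.16)/60) = 0.0645
- (0.10 − 1.960 × 0.0652)/0.0645 = −0.43
- Power = Φ(−0.43) = **33.3%**, against 78.9% stated

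Exact enumeration of the chi-square test gives 32.6%.

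**Step 2. Use all 131.** The same formula at 65.5 per arm gives **35.9%**. Exact enumeration gives 36.1% or 36.5%, depending on which arm has 66.

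**Step 3. Variants that might rescue the figure (90% versus 80%)**

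| Variant | Power |
|---|---|
| 60 per arm, unpooled variance | 34.1% |
| 60 per arm, arcsine | 34.3% |
| 60 per arm, continuity-corrected | 24.6% |
| 60 per arm, Fisher exact | 24.7% |
| 60 per arm, one-sided 0.05 | 45.5% |
| 120 per arm, two-sided | 58.4% |
| 120 per arm, one-sided | 70.2% (71.0% by arcsine) |

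None reaches 78.9%.

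**Step 4. Sample size needed for 78.9% power.** With z for 0.789 equal to 0.803:

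n = (1.960·√(2 × 0.85 × 0.15) + 0.803·√0.25)²/0.10² = 193.5, so **194 per arm, 388 in total**. With continuity correction it is 214 per arm, 428 in total.

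**Step 5. What 78.9% with 60 per arm does correspond to.** Hold 90% fixed and solve for the comparator: 70.0%. Check with p̄ = 0.80 and d = 0.20:

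- SE0 = 0.0730 and SE1 = 0.0707
- (0.20 − 1.960 × 0.0730)/0.0707 = 0.804
- Power = Φ(0.804) = **78.9%**

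The match is to that pair, not to 20-point differences in general. At 60 per arm, 80% versus 60% gives 67.0%, 85% versus 65% gives 72.1% and 95% versus 75% gives 87.6%.

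**Step 6. Precision.** The expected 95% CI half-width for the risk difference at 90% versus 80% is 1.96 × √(0.25/n). That is 12.7 points at 60 per arm and 12.1 at 65.5 per arm, both wider than the 10-point target.

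**Step 7. Non-response (assumed rates, since the article gives none).** Starting from 131, 10% non-response gives about 33% power, 15% about 31% and 30% about 27%.

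**The case against.** The arithmetic cannot be defended, but several points limit what should be drawn from it.

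- **The 90% versus 70% explanation is an inference.** The article mentions neither 70% nor a 20-point difference. This stands: the match is a likely source of the error, and the error does not depend on it.
- **Printing 90% versus 70% in the sample size section could look like a planning assumption that was never declared.** This stands. The authors should check their software output first and say which input was wrong.
- **The article already warns about power.** The limitations say full response is assumed and may not occur, and the Discussion anticipates that loss to follow-up may hinder statistical significance. Both attribute any shortfall to attrition, whereas power is about one third even with complete response. The caveats do not disclose the problem.
- **The figure for 131 is conditional.** The article does not say whether the participants added for the pilot enter the primary analysis. If they do not, 33% applies rather than 36%.
- **The Data Analysis Plan reports adjusted odds ratios.** Replacing them with a risk difference as the main result would change the primary effect measure after data collection. This stands: a risk difference should only be supplementary.
- **No passage says a null result will be read as equivalence.** True; that misreading is a risk, not a stated intention.

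**Conclusion.** The power statement is wrong as written. For 90% versus 80%, 1:1 allocation and a two-sided alpha of 0.05, 120 participants give about 33% power, some 45 points below the stated 78.9%. With all 131 analysed it is about 36%. The stated power would need 388 participants, more than three times 120 (388/120 = 3.2). These figures use only the article's own inputs and assume complete response at week 16; any non-response lowers them. The link to 90% versus 70% is a probable explanation, not an established fact. Because enrolment is complete, the consequence is for honest reporting and interpretation of the primary result, where it matters a good deal.

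**What to change.** 1. Check the EPIDAT output and state which input differed from the published 90% and 80%.
2. Correct the power statement in the abstract and in Sample Size Determination. Suggested wording: *With 120 participants (60 per arm) and a two-sided alpha of 0.05, power to detect 90% versus 80% adherence is about 33%; with all 131 analysed it is about 36%. Both figures assume complete response at 16 weeks.* If the output confirms it, add that 78.9% was obtained for 90% versus 70% with 60 per arm, and identify this as an input error, not as the planned effect.
3. Say whether the participants added for the pilot phase are in the primary analysis, so that it is clear which figure applies.
4. Amend the limitations so that the sample size is no longer said to correspond to a 10-point difference. State that power is low even without attrition, and that a non-significant result will not be interpreted as no difference between message types.
5. Optionally, report the unadjusted risk difference with its 95% CI as a supplement, leaving the planned adjusted odds ratio as it is.

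The cost is a correction of wording and a less favourable power figure. No further enrolment, procedure or change to the primary analysis is required.

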### Outcomes

The primary outcome is ART adherence, measured by the SMAQ questionnaire at 16 weeks of intervention and adjusted for the effect of covariables. The SMAQ questionnaire evaluates medication adherence. It provides a dichotomic result of adherence (yes or no) and a semiquantitative estimate of adherence. >95% adherence is considered as “yes” and <95% as “no.”

The secondary outcomes are (1) ART adherence measured by the SMAQ Questionnaire at 4, 8, and 12 weeks of intervention; (2) loss to follow-up; (3) time of permanence in the study; and (4) metrics on the use of a bidirectional platform for intervention delivery.

Since the SMAQ provides a dichotomic result of adherence (yes or no), we will report the percentage of participants’ adherent to ART per study group at 4, 8, and 12 weeks of intervention.

To measure loss to follow-up, we defined it as either (1) participants not responding to messages for ≥30 continuous days since receiving the intervention and not responding to messages or questionnaires at the end of their intervention period (*t*=16), or (2) participants not responding to messages for ≥30 continuous days since receiving the intervention and not reading their messages until the end of their intervention period. We will measure it from the start of the delivery intervention until the completion of the study.

Time of permanence in the study will be measured from the first date of intervention delivery (baseline) until loss to follow-up or study completion (16 weeks). We will describe this result's median and interquartile range in both study arms.

To assess the use of the bidirectional platform, we will report frequencies, percentages, and means with an SD of messages and questionnaires programmed for sending, sent, received, read, and answered by participants. Also, the frequencies and percentages of different process indicators self-reported by participants.

### Data Collection

For this study, data collection and management use REDCap electronic data capture tools hosted at Universidad Peruana Cayetano Heredia [24]. The enrollment form collects participants’ baseline sociodemographic data, history of ART, strategies for taking ART, assessment of their adherence with the SMAQ, depression screening, stigma, an evaluation of their satisfaction with the health services provided at the study center, and a measurement of their knowledge about ART and adherence. For participants allocated to the self-designed messages arm, we also register their created messages in REDCap. In total, 4 members of the research team are involved in data collection. The PI trained them with mock interviews and a web-based course on using REDCap.

We used an intermediate Excel file hosted in a secured drive to schedule messaging and questionnaire delivery per participant through the web-based study platform. This file contains the identification codes, a list of messages, and the date and time of sending.

The web-based study platform collects CSV file data on every message and questionnaire scheduled, sent, received, read, and answered per participant and chat sessions with providers. The records include anonymous hour-dated logs of all conversation contents with participants, including reasons for adding, modifying, or eliminating messages in the self-designed group and responses to study questionnaires.

To obtain the total number of eligible patients who meet eligibility criteria, independent of whether they are invited to participate, we collect routine data from the study center regarding the number of outpatient consults and patients in the age group of interest who pick up ART during the study period.

### Data Management

All study data are stored in secure, password-protected platforms, with access restricted to the authors of this protocol. Members of the research staff review data collected at baseline to ensure accuracy and completeness. Weekly, we download CSV files and reports from the web-based study platform. To ensure the records' accuracy, we compare a subset with the corresponding intermediate Excel file containing messages and questionnaires scheduled for delivery. Data curation will be performed at the end of the trial to point out missing values, identify any measurement outside the expected range, and evaluate strategies for mitigating these occurrences.

### Data Analysis Plan

The primary outcome variable is ART adherence, primarily measured as a binary variable defined by the SMAQ results at 4, 8, 12, and 16 weeks of intervention. For the analysis of the primary outcome, and with an intention-to-treat approach, we will compare between both study groups the proportion of participants adherent to ART at 16 weeks of intervention with bivariate (chi-square) and multivariate (logistic regression) analyses. We will build the multivariate logistic regression model with a stepwise approach (forward selection and backward deletion), adding 1 explanatory variable at a time and starting with the explanatory variables with the highest theoretical value and strength of association with the primary outcome in bivariate analyses. At each step of model building, we will check variations in the reported odds ratios and standard errors to define the retention or removal of explanatory variables. Irrespective of bivariate association, the study group variable and potential confounders, notably history of ART abandonment, ART pick-up visits during the study period, and time of permanence in the study, will be entered into the model. We will test the final model fit with Hosmer and Lemeshow goodness-of-fit test and report results with adjusted odds ratios and 95% CIs. Preliminary outcome analyses will not be performed since they require multiple measurements, and the intervention is relatively short. We will not perform multiplicity adjustments.

With mixed models for repeated measures, we will explore the changes in ART adherence, as determined by SMAQ, from baseline to 4, 8, 12, and 16 weeks on the intention-to-treat population, with no imputation of missing data. In this model, the change from baseline value will be the dependent variable, with participant random effect and baseline ART adherence, intervention group, and measurement time as the primary fixed factors. We will check linearity assumptions for time and use participants’ unstructured covariance structure. Two-sided 95% CIs for the mean change within each study group will be calculated.

To compare the time of study permanence in both study groups, we will perform survival analysis and compare hazard ratios for study loss to follow-up between study groups, according to the study definitions. This definition lets us know how many participants are active each week of intervention.

Additionally, we will perform a descriptive analysis of participants’ baseline characteristics overall and by study groups. We will also report the percentage of participants adherent to ART per study group at 4, 8, and 12 weeks of intervention. We will describe the characteristics of the intervention delivery, including the frequencies and percentages of messages received, read, and answered by participants. We will conduct all these analyses, blinding the study groups.

We will perform a thematic analysis of the most common themes in self-designed messages to evaluate relevant qualitative outcomes. In addition, we will report the median number of messages created by participants and the main reasons for adding, modifying, or eliminating messages.

We will report the results following the CONSORT-EHEALTH (Consolidated Standards of Reporting Trials of Electronic and Mobile Health Applications and Online Telehealth) statement for randomized controlled trials [25].

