## Discussion

Guided by the application of BCTs, we hypothesize that self-designed messages may be more effective in improving adherence to ART than standardized messages. Therefore, we aim to evaluate the effectiveness of a mobile phone messaging intervention with WhatsApp to improve adherence to antiretrovirals in young people living with HIV who receive routine HIV care at a public health facility in Lima and assess if there is a difference in effectiveness between the 2 types of messages tested. In a setting with still inceptive use of mHealth, our study protocol will provide valuable information on associations between several covariables, ART adherence, and participants’ experience with our pilot mHealth intervention.

Self-designed messages offer customization features that may enhance participant engagement with the intervention and increase its efficacy [26,27]. Therefore, we expect participants in the self-designed messages arm to have improved adherence compared to the standardized messages arm. Some subgroups may benefit more from the intervention, although it is beyond the scope of this study to compare differences between study arms and potential effect size. Given the potential personal customization component, we hypothesize that the self-designed arm will have an increased median time of permanence in the study and lower loss to follow-up. We also anticipate that loss to follow-up may hinder the statistical significance of results for the primary outcome and ART adherence measured at 4, 8, and 12 weeks of intervention for both study arms.

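### The week-16 primary comparison is labelled intention-to-treat, but no rule counts participants without a week-16 SMAQ, so as written it defaults to responders although loss is expected to differ by arm

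*Protocol article*

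**What the plan says.** In the Data Analysis Plan, the primary analysis is set out thus: "with an intention-to-treat approach, we will compare between both study groups the proportion of participants adherent to ART at 16 weeks of intervention". The methods are a chi-square test and a multivariable logistic regression on that single time point. The section gives no rule for a participant without a week-16 SMAQ. Its one explicit statement on missing values, "on the intention-to-treat population, with no imputation of missing data", belongs to the exploratory mixed model for repeated measures.

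Under Study Procedures—Implementation Phase, "participants receive WhatsApp questionnaires every 4 weeks after enrollment", and no other route for the follow-up SMAQ is described. The same section says that a participant who withdraws from the intervention is registered as withdrawn, "and no more messages will be sent". Ethical Considerations adds only that data gathered up to withdrawal may be used.

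The Discussion expects incomplete outcome data. The sample size was set "under the assumption that participants will respond to the final adherence questionnaire, which may not be the case". It also expects a difference between arms: "we hypothesize that the self-designed arm will have an increased median time of permanence in the study and lower loss to follow-up". The consequence it names is loss of significance: "We also anticipate that loss to follow-up may hinder the statistical significance of results for the primary outcome". Data Management says that end-of-trial curation will identify missing values and "evaluate strategies for mitigating these occurrences".

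**The concern.** An intention-to-treat comparison needs an outcome, or a stated way of handling its absence, for everyone randomised. Here the outcome arrives through the intervention's own channel, so a participant who disengages from the messages is also likely to have no week-16 SMAQ. A chi-square test and a logistic model at one time point leave such participants out unless a rule says otherwise.

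Disengagement is plausibly linked to poor adherence. If so, dropping non-responders raises the apparent adherence of both arms, and raises it more in the arm that loses more people. Under the article's own hypothesis that is the standardized arm, so the responder comparison would be tilted against the self-designed arm. The Discussion mentions significance and sample size but not this bias. Because the strategy is left to curation, the rule could be settled after the outcome data exist.

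**Working it through.** **Inputs from the article.** Planned adherence is 90% (self-designed) versus 80% (standardized), from Sample Size Determination. Allocation is 1:1 with 131 enrolled, so about 65 per arm. Loss is expected to be lower in the self-designed arm, with no size given.

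**Inputs assumed, because the article gives none.** Non-response at week 16 is m = 10-15% in the self-designed arm and 20-30% in the standardized arm. Adherence among non-responders is q = 40-50%, the same in both arms.

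**Formula.** If true adherence among all randomised in an arm is P, then P = (1 - m) × responder adherence + m × q. Hence responder adherence = (P - m × q) / (1 - m).

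**No true effect (P = 80% in both arms).**

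| Non-response, self-designed vs standardized | q | Self-designed responders | Standardized responders | Apparent difference |
|---|---|---|---|---|
| 15% vs 20% | 50% | (0.80 - 0.075)/0.85 = 85.3% | (0.80 - 0.10)/0.80 = 87.5% | -2.2 points |
| 10% vs 20% | 50% | (0.80 - 0.05)/0.90 = 83.3% | 87.5% | -4.2 points |
| 15% vs 25% | 50% | 85.3% | (0.80 - 0.125)/0.75 = 90.0% | -4.7 points |
| 10% vs 30% | 40% | (0.80 - 0.04)/0.90 = 84.4% | (0.80 - 0.12)/0.70 = 97.1% | -12.7 points |
| 20% vs 20% | 50% | 87.5% | 87.5% | 0 |

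The first and fourth rows are the mildest and most severe corners of the assumed range.

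**True effect of +10 points (90% vs 80% among all randomised).**
- 15% vs 20%, q = 50%: (0.90 - 0.075)/0.85 = 97.1% against 87.5%, so +9.6.
- 15% vs 25%, q = 50%: 97.1% against 90.0%, so +7.1.
- 10% vs 30%, q = 40%: (0.90 - 0.04)/0.90 = 95.6% against 97.1%, so -1.6.

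**The opposite rule.** Suppose adherence among responders is 80% in both arms and every non-responder is counted as non-adherent. With 10% vs 20% non-response the result is 0.80 × 0.90 = 72% against 0.80 × 0.80 = 64%, a difference of +8 points. With 10% vs 30% it is 72% against 56%, or +16. The two simplest rules push in opposite directions, by amounts comparable with the planned 10 points, so the choice between them cannot be left open.

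**The case against.** A reader might infer that the plan restricts the primary analysis to week-16 responders. It does not say so. Chi-square and logistic regression are equally compatible with imputed outcomes or with non-response counted as failure, and the no-imputation wording covers only the mixed model. Responders-only is what the plan defaults to, not a rule it states.

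It can also be argued that handling of missing outcomes belongs in a statistical analysis plan that is not shown. Silence alone would indeed be no finding. But the article is not silent: it defers missing-value strategies to curation, describes outcome collection that ends with withdrawal from the intervention, and names an expected difference between arms while treating loss only as a matter of significance. The curation sentence is general, also covering out-of-range values, and does not prove that the primary rule will be chosen after the fact.

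Several mitigating points stand:
- The Data Analysis Plan says analyses will be run with study groups blinded. The scope of that sentence is unclear, but it reduces the room for a choice driven by results.
- The mixed model can use partial data from weeks 4 to 12, and loss to follow-up is compared between arms.
- The hypothesis on loss uses the definition under Outcomes (at least 30 days of non-response plus a further condition), which overlaps with a missing week-16 SMAQ but is not identical to it.
- The severe corner needs 97.1% adherence in standardized-arm responders against 40% in non-responders.

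A reader might further infer that participants not taking ART cannot be scored on the SMAQ and drop out as missing. ART use is not an inclusion criterion and current intake is a stratification factor, but the article does not give the SMAQ items, so this is not supported.

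**Conclusion.** The point holds in a limited form. The article labels the primary comparison intention-to-treat, collects its outcome through the intervention channel, expects loss that differs by arm, and fixes no way to count participants without a week-16 SMAQ. Followed as written, it yields a responder comparison. That comparison is biased if non-response is linked to non-adherence and differs by arm. The second condition is close to the article's own hypothesis; the first is plausible but not stated.

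Under the assumed rates, the bias with no true effect is about -2 to -13 points, against a planned difference of 10, and a true +10 appears as +9.6 to -1.6. These figures illustrate sensitivity; they do not predict the trial's result. This should be corrected before the arms are compared.

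**What to change.** Before any comparison by arm, and with group labels still masked:

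1. Define the primary analysis set as all randomised participants.
2. Fix one primary method for a missing week-16 SMAQ. One option is multiple imputation using arm, the baseline and week 4, 8 and 12 SMAQ, the four stratification factors and ART pick-ups. Keep the model simple: with about 65 per arm and 10-20% expected to be non-adherent, there are only about 7 to 13 non-adherent participants per arm.
3. Add two sensitivity analyses: non-response counted as non-adherent, and a tipping-point analysis by arm.
4. Report week-16 SMAQ completion by arm.
5. State how participants recorded as not taking ART are classified for the primary outcome.
6. Separate withdrawal from messages from withdrawal from follow-up only if follow-up is still open. It was due to end in November 2024 and curation was under way in February 2025, so this is probably too late.

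The cost is some extra analysis work on data already planned for collection. Imputation also brings a missing-at-random assumption, which the sensitivity analyses test.
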